#### Other measurements

During the baseline assessment, sociodemographic information will be collected, such as gender, relationship, level of education, and work. Furthermore, details of the patients’ own clinical history of addiction as well as of their family will be asked. Next, participants who are assigned to one of the training conditions will be asked about their expectations of the intervention. Before and after each training session, participants will rate their intensity of craving on a visual analogue scale (VAS), varying from 0 (no craving at all) to 100 (extreme craving). With this, possible direct effects of the intervention on subjective craving can be examined. Furthermore, at the end of the baseline assessment, all participants are asked to fill in a short questionnaire about their computer/laptop use in their private life. This information might be helpful when investigating for whom this iABM intervention was effective. Last, after the first week of training and during the post-assessment, participants, who are assigned to one of the training conditions, will be asked to fill in an evaluation questionnaire, in which they can give their opinion about the intervention and are asked to indicate whether the intervention helped them. Information derived from these questionnaires can be used as indications for possible next steps towards implementation. For an overview of all questionnaires and tasks per time point, see Table 2.

**Table 2 Tab2:** Overview of measurement instruments per time point

Purpose	Measures	Baseline	Post-assessment	Follow-up
Attentional bias assessment	Odd one out task	X	X	X
Baseline measures	Demographics	X		
	History of addiction	X		
	Family history of addiction	X		
Primary outcome measures - clinical	MATE (substance use, craving)	X	X	X
	Clinical state (relapse)			X
Primary outcome measures - Societal/economical	TiC-P	X	X	X
	EQ-5D	X	X	X
Secondary outcome measures	MATE (depression, anxiety and stress)	X	X	X
	Computer use	X		
Others	Expectation-questionnaire	X^a^		
	Training evaluation		X^a^	

^a^only to be filled in by participants in one of the training conditions

### Primary and secondary outcome measures

The effectiveness of the iABM intervention will be examined by changes in substance use (i.e. quantity of use in the past 30 days), craving, and relapse rates. Measurements of attentional bias will serve as a manipulation check for the effects of iABM intervention.^1^ Secondary outcome measures are cost-effectiveness,^2^ and secondary physical and psychological complaints (depression, anxiety, and stress). The evaluation forms of the patients and therapists will be assessed as well.

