### Participants and procedure

Participants will be treatment-seeking adult patients diagnosed with alcohol use disorder (AUD) or cannabis use disorder (CUD) with an indication for TAU in addiction care as described above. Recruitment will take place at the four addiction care centres. The therapists will inform all their patients during the intake or the first session of TAU about the possibility of participating in a study. Interested patients will receive a folder, containing a leaflet from the Dutch government about scientific research in general, a patient information letter with specific information about the current study, an informed consent form with envelope, and a small card with contact information of the studies’ helpdesk. If patients give permission to their therapist, he/she will forward the patients’ contact information to a researcher, who will call them a few days later in order to screen for eligibility and to give a brief oral explanation about the study rationale and the norms of data processing. Thus, recruitment will be done by the researchers, while the therapists are responsible for providing the first information to their patients. Patients will be included if they (a) are 18 years or older, (b) have a main diagnosis of AUD or CUD, and (c) have an indication for TAU in addiction care as described above. A contra-indication for participation is (a) a problem with compulsive gaming, gambling disorder, or internet addiction as measured with a short version of the C-VAT 2.0 [42] and/or (b) the absence of a personal computer or laptop and/or no access to internet. Eligible patients who decide to participate will be asked to sign the informed consent form and to send it to the researcher. After receiving the signed informed consent form, they will be assigned to the online registration and monitoring tool of the study. The signed informed consent form needs to arrive at the researchers’ office within the period of the first three sessions of TAU. Otherwise the potential participant is excluded from the study, as early effects of TAU could distort pre-measures too much.

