#### Questionnaires

Participants’ general health state is assessed by means of the EuroQol-5D-3 L questionnaire [49]. Health care-related costs are evaluated with the Treatment Inventory of Costs in Psychiatric Patients questionnaire [50]. The Measurements in Addiction for Triage and Evaluation questionnaire [51] is a standard instrument in the Dutch addiction care and will be completed during the intake and at the end of the treatment through the therapists. During the 6 and 12 month follow-up measurements, the same questions will be asked online. For this study, the following parts of the MATE will be evaluated: substance use, the Obsessive-Compulsive Drinking Scale (OCDS5), and the Depression Anxiety Stress Scale (DASS).

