### Randomization

Participants who meet the inclusion criteria will be automatically assigned to one of the three conditions with the following likelihood (1) 50% TAU + iABM, (2) 25% TAU + placebo condition and (3) 25% TAU-only. Furthermore, the registration and monitoring system stratifies for gender, age group (18–30, 30–50, 50+), type of addiction, and institution. Therefore, participants are assigned to one of the three conditions to which the fewest participants of their gender, age group, and type of addiction are assigned accounting for the institution of the participants. When proven effective, participants in the control conditions (TAU + placebo condition and TAU-only) will be offered the iABM intervention after the end of the study (approx. End 2018).

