### Data analyses

#### Clinical analysis

First, changes in attentional bias, as measured with the *odd one out task*, will be examined by using a 4 (within subjects: pre, post, FU1, FU2) × 2 (between subjects: TAU + iABM versus control conditions) repeated measure ANOVA, with attentional bias as dependent variable. To assess the validity of the main hypothesis, a 4 (within subjects: pre, post, FU1, FU2) × 2 (between subjects: TAU + iABM versus control conditions) repeated measure ANOVA will be conducted to examine the effects of the iABM intervention on substance use and craving, as measured with the MATE. In order to evaluate the effects of iABM intervention on rates of relapse, a Cox regression analysis will be conducted to model the time until relapse occur.

Further, changes in secondary physical and psychological complaints (depression, anxiety and stress) will be tested by a 4 (within subjects: pre, post, FU1, FU2) × 2 (between subjects: TAU + iABM versus control conditions) repeated measure ANOVA, based on the MATE. Missing data will be handled with multiple imputation.

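### Quantity of use is pooled over alcohol and cannabis patients with no common scale and no addiction-type term, so the substance with the larger numeric spread dominates this primary outcome

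*Protocol article*

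**What the plan says.** All references are to the protocol article.

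- **Population.** Under Participants and procedure, patients must "have a main diagnosis of AUD or CUD". Both diagnoses enter one trial.
- **Outcome.** Primary and secondary outcome measures bases effectiveness on "changes in substance use (i.e. quantity of use in the past 30 days), craving, and relapse rates". The abstract and Table 2 also list substance use as primary.
- **Instrument.** Questionnaires takes substance use from the MATE: "the following parts of the MATE will be evaluated: substance use, the Obsessive-Compulsive Drinking Scale (OCDS5), and the Depression Anxiety Stress Scale (DASS". No unit of quantity and no conversion between substances is given.
- **Model.** In Clinical analysis, a "repeated measure ANOVA will be conducted to examine the effects of the iABM intervention on substance use and craving, as measured with the MATE". The factors are four time points and one two-level contrast, "between subjects: TAU + iABM versus control conditions". No other factor or covariate is named.
- **Allocation.** Under Randomization, the system "stratifies for gender, age group (18–30, 30–50, 50+), type of addiction, and institution".
- **Sample size.** 64 patients in each of the treatment and control arms, for a medium effect with power 0.8 at alpha 0.05, raised to 213 in total for 40% dropout. There is no split by substance.

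**The concern.** An amount of alcohol and an amount of cannabis have no natural shared unit. If both are entered as recorded into one dependent variable, the mean change in each arm mixes two kinds of quantity and cannot be read as either. The weight each group carries then depends on the numerical spread of the unit in which its substance was recorded, not on how many patients it has or how much they benefit.

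Two consequences follow. First, the sample size assumes a medium standardised effect on one scale, and pooling unequal scales shrinks that effect even when both groups benefit equally. Second, a benefit confined to the smaller-spread substance can disappear in the pooled test. A positive or null result on this outcome could not then be interpreted for either population.

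Elsewhere the protocol treats the substance as important. The training and the attentional bias task have separate versions by diagnosis, and allocation is balanced on it. The distinction is lost only in the outcome and the model.

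**Working it through.** **1. The plan's own figure.** Taking a medium effect as d = 0.5, a two-sided two-sample t-test at alpha 0.05 with power 0.80 needs 63.77, so 64 per arm. Power at 64 per arm is 0.801. Dropout: 128 / (1 − 0.4) = 213.3, stated as 213. The sample size reproduces, on one common scale.

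**2. Inputs not in the documents (assumptions).** Let p be the alcohol share, R the SD of alcohol quantity divided by the SD of cannabis quantity as recorded, with the cannabis SD set to 1. The true effect is 0.5 SD within each substance and 64 patients per arm are evaluable. Only the inequality of scale is modelled. The t-test stands in for the test of change; it is not the full four-occasion ANOVA.

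**3. Formulas.**

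- Pooled mean difference = 0.5(pR + 1 − p)
- Pooled variance = pR² + 1 − p
- Pooled d = 0.5(pR + 1 − p) / √(pR² + 1 − p)
- Alcohol's part of the difference = pR / (pR + 1 − p)
- Pooled d for an effect in cannabis patients only = 0.5(1 − p) / √(pR² + 1 − p)

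Worked case, p = 0.5 and R = 5: difference 0.5 × 3.0 = 1.5; variance 12.5 + 0.5 = 13; d = 1.5 / 3.606 = 0.416; power 0.65; alcohol's part 2.5 / 3.0 = 83%. Cannabis only: 0.25 / 3.606 = 0.069, power 0.07.

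**4. Results.**

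| Cannabis share | R | Pooled d | Power, effect in both | Difference from alcohol | Power, effect in cannabis only |
|---|---|---|---|---|---|
| 30% | 3 | 0.467 | 0.75 | 88% | 0.06 |
| 30% | 5 | 0.450 | 0.72 | 92% | 0.06 |
| 30% | 10 | 0.435 | 0.69 | 96% | 0.05 |
| 50% | 3 | 0.447 | 0.71 | 75% | 0.10 |
| 50% | 5 | 0.416 | 0.65 | 83% | 0.07 |
| 50% | 10 | 0.387 | 0.58 | 91% | 0.05 |

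**5. After scaling within substance (R = 1).** With the effect in both groups, d = 0.50 and power is 0.80. With the effect in cannabis patients only, d = 0.5 × 0.3 = 0.15 or 0.5 × 0.5 = 0.25, and power is 0.13 or 0.29.

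**6. Spread the other way round.** With p = 0.7, R = 0.2 gives alcohol 32% of the difference and power 0.58; R = 0.1 gives 19% and 0.47. Cannabis then dominates.

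**The case against.** - **It may be left to the SAP.** An article commonly leaves covariate lists and outcome scaling to the SAP, which is not shown. This stands for gender, age group and institution: their absence from the stated model is not a contradiction, and omitting balancing factors usually makes standard errors conservative. It does not dispose of the main point. The article names the outcome as a quantity and gives the model with its exact factors; followed as written, these pool amounts with no shared unit.
- **Alcohol need not dominate.** A reader might infer that alcohol drives the result. The documents give no units, SDs or case mix, and step 6 of the working shows that dominance can reverse.
- **Level differences cancel.** A reader might say that between-substance variance inflates the error term. The outcome is change, and the time by condition test uses within-patient error, so stable differences in level between substances drop out. Adding a mean gap between substances equal to the gap in their SDs would lower power further, for example to 0.45 at R = 10 with equal shares. That loss does not apply to the test of change. What remains is unequal spread of change and any difference between substances in its course over time.
- **Other outcomes are unaffected.** Craving is a questionnaire score, attentional bias is a reaction-time difference in the same unit for both task versions, and relapse is modelled as time to event. It would be wrong to call the trial's primary results uninterpretable as a whole: one of three effectiveness outcomes is affected.

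**Conclusion.** The point holds for substance use and only there. As written, the analysis yields a pooled mean change without an interpretable unit, weighted towards whichever substance has the larger numeric spread. The documents do not show which substance that is.

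This conclusion follows from the stated outcome and model. The size is illustrative and rests on the assumed SD ratio of 3 to 10, cannabis share of 30 to 50% and common true effect of 0.5 SD. Power for this outcome is then about 0.58 to 0.75 against the intended 0.80. In this illustration, where cannabis has the smaller spread, an effect confined to cannabis patients is found about 5 to 10% of the time, against 13 to 29% after within-substance scaling. If the spreads are close, the loss of power is small (0.77 at R = 2 with a 30% cannabis share), but the missing unit remains.

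**What to change.** For the substance-use outcome:

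1. Define quantity on a unit-free scale, for example the 30-day quantity divided by the baseline SD of that patient's substance. Any log-based version needs a stated rule for zero use, because a log ratio is undefined for abstinent patients.
2. Add type of addiction to the model with its time and condition interactions, including time by condition by type. A main effect of type alone removes level differences but leaves the treatment effect on two scales.
3. Report the effect for each substance with its confidence interval, next to the pooled scaled effect. These are estimates, not powered tests: at d = 0.5, 32 patients of one substance per arm give power 0.50, and 19 give 0.32.

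As a secondary improvement, include the balancing factors (type of addiction, gender, age group, institution) as covariates in the clinical models.

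The variables are already collected or held in the allocation system. The cost is analysis wording and a few degrees of freedom; recruitment and assessments do not change.

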### Sample size

To find a difference between groups of medium effect size with a power of 0.8 at an alpha of 0.05, both the treatment and the control arm need to include 64 patients, as calculated with.

G*power 3.1.5. Dropout rates in regular addiction treatment are known to be approximately 20%. Given the 6 and 12 months follow-up measurements a dropout rate of 40% was calculated. Therefore, a total amount of 213 patients will be recruited.

### Withdrawal

All participants can withdraw from the study at any time. However, they are asked whether they are willing to complete the measurements. Thus, even if participants stop the training (iABM intervention), they are still invited to participate in the post-assessment and follow-up assessments.

### Randomization

Participants who meet the inclusion criteria will be automatically assigned to one of the three conditions with the following likelihood (1) 50% TAU + iABM, (2) 25% TAU + placebo condition and (3) 25% TAU-only. Furthermore, the registration and monitoring system stratifies for gender, age group (18–30, 30–50, 50+), type of addiction, and institution. Therefore, participants are assigned to one of the three conditions to which the fewest participants of their gender, age group, and type of addiction are assigned accounting for the institution of the participants. When proven effective, participants in the control conditions (TAU + placebo condition and TAU-only) will be offered the iABM intervention after the end of the study (approx. End 2018).

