### Blinding

Since all assessments take place online, thus in the absence of the researchers, the outcome data are blinded. However, one researcher will be aware of the condition of the participants in order to support them appropriately when technical or personal problems appear. It is unlikely that this will entail problems of bias, as the researcher is not involved in any measurement and the motivational part of the study lies in the responsibility of the therapists. The therapists and participants will be blinded for the two training conditions. Therefore, the iABM intervention and the placebo condition were designed such that the use of the same task stimuli would be possible, making both conditions look very similar. Furthermore, it is unlikely that participants will tell their therapists much about the content of the training, but more about whether they train regularly or whether they like or dislike the training. This will help to keep the therapists blinded. Furthermore, the therapists will be instructed not to do any ‘research’ about what might be the ‘real’ intervention. Participants will be asked to indicate their expectation about their condition in the post-assessment.

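### As printed, the fewest-participants assignment rule contradicts the 50/25/25 allocation and, if coded that way, moves the trial to about 1:1:1 with power near 0.76

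*Protocol article*

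**What the plan says.** The Randomization section sets the target as "1) 50% TAU + iABM, (2) 25% TAU + placebo condition and (3) 25% TAU-only". It then says that the registration and monitoring system stratifies for gender, age group (18–30, 30–50, 50+), type of addiction and institution, and that for this reason participants are "assigned to one of the three conditions to which the fewest participants of their gender, age group, and type of addiction are assigned", with institution taken into account.

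Other sections rely on the 50/25/25 target:
- Trial design describes a two-armed trial whose control arm is divided into placebo and TAU-only.
- Sample size says that "both the treatment and the control arm need to include 64 patients", that is, 1:1.
- Clinical analysis compares iABM with the two control conditions pooled.

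On who could see allocations, Participants and procedure says "recruitment will be done by the researchers", and Blinding says "one researcher will be aware of the condition of the participants", in order to give support when problems arise.

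**The concern.** Under a 50/25/25 target, iABM should normally hold the most patients of any type. A rule that always picks the condition with the fewest similar patients therefore steers patients away from iABM whenever the target is being met. Take a group of similar patients standing exactly on target at 10:5:5. The printed rule sends the next ten to placebo and TAU-only, until the counts are 10:10:10. The ratio and the rule cannot both govern the same assignments unless the counts are weighted by the ratio, and the text does not say that they are.

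Two things are at stake. One is the 1:1 split between iABM and pooled control on which the sample size rests. The other is predictability: the rule as stated has no chance component, so wherever one condition is strictly lowest, the next assignment follows from the existing counts.

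**Working it through.** **Inputs from the protocol article (Sample size, Randomization).** Power 0.80, alpha 0.05, a medium effect, 64 per arm, 40% dropout, 213 recruited, target 50/25/25. The balancing factors give 2 × 3 × 2 × 4 = 48 full cells.

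**Assumptions.** Medium effect means d = 0.5 and the test is two-sided; neither is printed, but together they reproduce the stated 64. Patient mixes for the simulation are also assumed: a 65/35 or 70/30 gender split, age 30/45/25 or 20/50/30, substance 70/30, four equal centres. The results hardly differ between mixes.

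**1. The plan's own figure.** Two-sample t-test with noncentrality d·√(n₁n₂/(n₁+n₂)) and n₁+n₂−2 degrees of freedom.
- Solving for 0.80 gives 63.8, so 64 per arm. At 64 v 64 the noncentrality is 0.5·√32 = 2.83 and power is 0.801.
- Recruitment: 128/(1−0.40) = 213.3, stated as 213. Both figures reproduce.

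**2. Allocation under the rule as printed** (213 patients, 300 simulated trials per reading).

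| How similar patients are counted | Mean iABM:placebo:TAU-only | Assignments fixed by existing counts |
|---|---|---|
| Marginal totals over the four factors | 71:71:71 | about 75% |
| Marginal totals within institution | 71:71:71 | about 66% |
| Within the 48 full cells, ties broken 2:1:1 | about 76:68:69 | about 26% |
| Within the 48 full cells, ties broken equally | 71:71:71 | about 26% |

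Full cells hold only about 213/48 = 4.4 patients each, so ties are frequent. That is why the tie-break matters there and why fewer assignments are determined.

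**3. Power under those splits, after 40% dropout.**
- 71 v 142 recruited: 71 × 0.6 = 42.6 and 142 × 0.6 = 85.2, about 43 v 85. Noncentrality 0.5·√(43·85/128) = 2.67, power 0.755.
- 76 v 137 recruited: 45.6 and 82.2, about 46 v 82. Noncentrality 0.5·√(46·82/128) = 2.71, power 0.768.
- Restoring 0.80 at 1:2 needs 48 + 96 = 144 evaluable (noncentrality 2.83 again), or 144/0.6 = 240 recruited, 27 more than planned.

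**4. The same rule on ratio-weighted counts** (iABM count divided by 2, the others by 1, ties 2:1:1).
- iABM receives about 106 (marginal), 105 (marginal within institution) or 99 (full cells) of 213.
- The least favourable, 99 v 114, leaves 59.4 v 68.4 evaluable, with power 0.799.
- Weighting alone does not add chance: about 81%, 74% and 39% of assignments are then fixed by the counts on the three readings.

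**The case against.** The strongest reply is that the section opens with the governing ratio, expressed as a likelihood, and that fewest may be meant relative to it. Ratio-weighted minimisation would satisfy both sentences and keep power at about 0.80. That stands. The document does not show that the trial loses its split, only that the printed rule would lose it.

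A second reply is that a journal article may leave weighting, tie-breaking and assignment probability to the full protocol or system specification. This stands for a detail that is merely absent. It does not cover the main point, because the article prints a specific rule and that rule conflicts with its own ratio.

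Third, the effect is modest. Power falls by about 3 to 5 points, unequal allocation biases nothing in itself, and the figures are for a two-sample t-test, not the planned repeated-measures ANOVA. All of that is correct.

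Fourth, a reader might combine the Blinding and Participants and procedure sections and conclude that a recruiter who knows earlier allocations can predict the next one, so that the trial is not properly randomised. The documents do not support this. Nowhere is the researcher who knows the conditions said to be a recruiter or to see live counts. Assignment is automatic, and patients enter the online system only after signed consent has arrived. How far the rule is deterministic also depends on how counts are formed. What remains is a predictability risk, because no chance component is stated and nothing says that this researcher is kept out of enrolment.

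**Conclusion.** The contradiction is on the page: the target is 50/25/25, but the stated rule, with unweighted counts, leads to about 1:1:1. The consequence depends on what the system does.
- If it is coded as printed, the primary comparison has about 43-46 v 82-85 evaluable patients and power of about 0.76-0.77 instead of 0.80. This rests on d = 0.5, a two-sided test, 40% dropout in every condition and the assumed patient mix.
- If it already weights the counts 2:1:1, the split and the power are essentially as planned and only the wording needs correcting.

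Between about 26% and 75% of assignments under the printed rule would be determined by existing counts. That calls for a stated random element; it does not show that selection bias occurred. The age bands meet at 30 and 50, which is a minor labelling fault.

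**What to change.** 1. State and code the rule on ratio-weighted counts: iABM count divided by 2, placebo and TAU-only counts divided by 1, assigning to the lowest.
2. Add a random element: assign the most under-represented condition with a stated probability below 1, and break ties 2:1:1. Weighting alone does not supply this.
3. Say whether institution is a stratum or one of the balancing factors.
4. Verify the coded algorithm against 50/25/25 by simulation.
5. Make the age bands non-overlapping, for example 18–29, 30–49 and 50+.

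If equal three-way allocation is really used, correct the 50/25/25 statement and restate power as about 0.76, or raise recruitment to about 240 to keep 0.80.

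The cost is a configuration check or change in the online system and one paragraph of text. The downside is marginally looser balance on the factors.
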